GLMM is a flexible analytic approach with wide use in the health sciences (82). Mixed model regression allows for repeated measures across individuals by modeling the correlation among the repeated measures. GLMM can accommodate a range of correlation structures among the measures, as well as continuous and discrete outcome distributions, unbalanced designs, different link and variance functions, and, in the case of the analysis of independent data, is equivalent to logistic, ordinary least squares regression, or analysis of covariance modeling.

For the GLMM, first we will assess the covariance structure of the data so that inferences about means are valid. We cannot assume that repeated measures for an individual will be equally correlated because two measurements taken at adjacent times may be more highly correlated than two measurements taken several time points apart. To select the best method for modeling the repeated measures, we will use the methods of Wolfinger (83) and statistics such as Akaike's and Schwarz's information criteria.

After determining the appropriate covariance structure, we will develop longitudinal models of the effect of intervention condition on post-intervention (follow-up) criterion measures that take into consideration the baseline values for the corresponding criterion measure as well as important covariates. Mixed model parameter estimates and tests will allow us to compare intervention effects and to examine intervention effects over the course of follow-up time

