points. Post-intervention follow-up criterion measures will be regressed onto study intervention condition, time of assessment, a polynomial function of time (for example, quadratic) if appropriate, and the measure of the criterion at baseline. In addition, we will add important covariates, including adaptive randomization variables and selected demographic variables, such as ethnicity and education, as well as suitable baseline health-related variables and medical characteristics. Tests of the interaction of intervention condition with time of measurement will be evaluated to determine whether the effect of intervention condition varied as a function of time. In the case of statistically significant interactions of intervention condition with time, tests of the effect of intervention condition will be conducted at each individual time point. We will use Bonferroni corrections for each set of multiple comparisons where appropriate. Standard methods of model diagnostics will be used to identify influential observations and to determine suitable transformations where necessary.

We will compare compliance with acupuncture between patients randomized to the acupuncture and sham acupuncture groups. Compliance will be measured as the number of times the participants received their scheduled intervention per week. At each assessment after the end of radiotherapy, we will determine if patients in the two groups differ in the number of times they received their scheduled intervention (since the last analysis) using a Wilcoxon rank-sum test. We expect that these frequencies will not be normally distributed so we plan to use a nonparametric test. If there is a statistically significant difference or trend for significance in compliance between any two groups ( $p < 0.10$ ), we will also determine if there is a difference between other outcomes. We will use either t-tests or nonparametric tests such as the Wilcoxon rank-sum test to determine the significance of these differences.

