#### **c. Sample size calculations**

These precision and power estimates are based on a final post-intervention sample size of 300 study participants, 100 in each of the three intervention groups. To achieve this post-intervention sample size, we will oversample by 31% (i.e., 435 participants) to account for attrition. That is, we will allow for up to a 31% drop- out rate.

Our primary analysis is a mixed model regression analysis with repeated measures to evaluate the between group differences across the post-intervention time points with adjustment for covariates. Assuming a two- sided significance level of 0.05, we will have at least 80% power to detect differences between any pair of group means of 0.4 standard deviation units (SD – Effect Size Index) across the three post-intervention time points. In addition, the detectable mean difference between groups is 0.49 SD units with a two-sided significance level of 0.01. In our previous study, we found differences on post-intervention XQ means ranging from 0.80 SDs at the end of radiotherapy to 0.68 SDs at 1 month when comparing the acupuncture group with the standard care group. The associated XQ average values for the two groups at 1 month post radiotherapy were: 32.2 (SD=10.6) for acupuncture group and 41.5 (SD=9.6) for control group. As we do not know the exact differences that will occur between the sham acupuncture group and the other two groups, and given the definition of clinically significant effects (i.e., effect sizes of approximately 0.5 SDs being argued to be clinically meaningful) (25, 86, 87) the current study is still well-positioned to detect clinically significant effects between groups that may be present. We prefer to justify sample size using a paired t-test for simplicity and because it is conservative approach, although the later analyses using repeated measures will have greater power to detect differences between groups.

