### C.10 Progress Report Since Last Review

The original application was submitted in June 2009. Since then, we have completed a 6-month follow-up of 70 of the original 85 patients from the randomized trial to examine the duration of the response. Although both groups had a reduction in xerostomia symptoms, the difference in XQ scores between groups remained about the same, with lower scores in the acupuncture group (acupuncture = 21.9 vs control = 34.0,  $p < 0.0006$ ). Examination of XQ scores of 30 or above using chi square analyses showed that by 6 months, the acupuncture group had significantly fewer patients with scores over 30 (acupuncture 27.6%; control 63.6%,  $p = 0.005$ ). The group differences in MDASI-HN scores also remained different (MDASI-HN Symptoms: acupuncture = 2.6 vs control = 4.6,  $p = 0.07$ ; MDASI-HN Interference: acupuncture = 2.6 vs control = 4.0,  $p = 0.02$ ). Importantly, 6 months after the end of radiotherapy, the measure of stimulated saliva flow indicated continued improvement for the acupuncture group (acupuncture = 1.57 vs control = 0.95,  $p = 0.003$ ). For unstimulated saliva flow, group means were in the expected direction but were not statistically significantly different (acupuncture = 0.50 vs control = 0.46,  $p = 0.60$ ). The proposed trial will allow us to follow a larger sample size out to 12 months to determine the stability of the response.

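### Time-point tests of mean XQ in the mixed model wait on an arm-by-time interaction for which no power is given, so the 10-15 month difference may have no planned contrast

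*Supplement*

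**What the plan says.** All references are to the Final Protocol in the Supplement.

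- **Interaction test** (C.6, a. Data analysis). The condition-by-time interaction in the mixed model is tested "to determine whether the effect of intervention condition varied as a function of time". The next step, testing at single visits, is conditional: "In the case of statistically significant interactions of intervention condition with time, tests of the effect of intervention condition will be conducted at each". Bonferroni corrections are then applied to sets of multiple comparisons where appropriate. Nothing is said about time-point contrasts when the interaction is not significant.
- **Correlation** (same section). The plan expects that "two measurements taken at adjacent times may be more highly correlated than two measurements taken several time points apart".
- **Tests outside the condition** (same section). Three-arm ANOVA of XQ at end of radiotherapy; binomial tests of XQ ≤30 and of CTCAE xerostomia at each follow-up, with a 0.003 level if 15 tests are made.
- **Sample size** (C.6, c. Sample size calculations). It rests on a "final post-intervention sample size of 300 study participants, 100 in each of the three intervention groups", with "at least 80% power to detect differences between any pair of group means of 0.4 standard deviation units". A second figure follows: "the detectable mean difference between groups is 0.49 SD units with a two-sided significance level of 0.01". Both concern group means. About 0.5 SD is taken as clinically meaningful.
- **Durability** (C.10). "The proposed trial will allow us to follow a larger sample size out to 12 months to determine the stability of the response".

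**The concern.** XQ is the primary outcome, and the C.10 sentence concerns how its benefit lasts. In the longitudinal model the only stated route to a mean XQ comparison at a single late visit runs through a significant interaction. Interaction tests generally have much less power than tests of main effects, and this one was not sized.

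If the arm effect averaged over visits is significant and the interaction is not, the plan yields one averaged effect. It then has no planned test or interval for the 10-15 month mean difference and none for how far the effect has changed. A benefit that had halved by then could go unexamined on the primary scale.

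**Working it through.** **1. The plan's own power figure.** Two-sample normal approximation, 100 per arm, unit SD, so the SE of a difference is √(2/100) = 0.1414.

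- 0.4 SD at two-sided 0.05: Φ(0.4/0.1414 − 1.96) = Φ(0.87) = 80.7%.
- 0.49 SD at two-sided 0.01: Φ(0.49/0.1414 − 2.576) = Φ(0.89) = 81.3%.

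Both stated figures reproduce. Neither concerns the interaction.

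**2. Inputs for the interaction test.**

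- From the plan: 100 evaluable per arm, three arms, alpha 0.05, a starting effect of 0.5 SD, and four time points from end of radiotherapy (end of radiotherapy, 2-4, 5-9 and 10-15 months).
- Assumed, because the documents do not give them: within-patient correlation, shape of decline, and the position of the sham arm (here equal to standard care).

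**3. Formula.** Let v be the arm difference at the four visits, Σ the within-patient correlation matrix and C the matrix of successive differences. With one arm shifted by v and two arms at zero, the between-arm sum of squares is 2/3 of v². Hence

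λ = 100 × (2/3) × q, with q = v′C′(CΣC′)⁻¹Cv, on (3−1)(4−1) = 6 df.

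The miss rate is the probability that a noncentral chi-square (6 df, λ) falls below 12.59.

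Worked case: v falls linearly from 0.5 to 0.25, compound symmetry (CS) 0.5. The steps are 0.0833, so the sum of squares of v about its mean is 0.0833² × 5 = 0.0347. Then q = 0.0347/(1 − 0.5) = 0.0694, λ = 66.7 × 0.0694 = 4.63, and the miss rate is 69%.

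**4. Results (miss rates).**

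| Structure | 0.5 → 0.25 SD: λ | Missed | 0.5 → 0 SD: λ | Missed |
|---|---|---|---|---|
| CS 0.5 | 4.63 | 69% | 18.5 | 8% |
| CS 0.7 | 7.72 | 49% | 30.9 | 0.5% |
| AR(1) 0.5 | 2.39 | 83% | 9.57 | 38% |
| AR(1) 0.7 | 3.17 | 78% | 12.7 | 23% |
| CS 0.8 | 11.6 | 28% | 46.3 | below 0.1% |

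The correlation decay that the plan expects points towards the AR(1) rows.

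**5. Sensitivity for the halving.** Varying the number of visits (three to five), the decline (linear, or a drop at the last visit only) and the sham arm (equal to standard care, or midway) gives about 33-88% over correlation 0.3-0.7. At CS 0.8 the lowest value is about 14%. In simulation of the halving case, the chance of a significant averaged group effect together with a non-significant interaction was 43-81% over the four structures with correlation 0.5 or 0.7.

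**6. Do the XQ ≤30 tests fill the gap?** Assume normal XQ, control mean 34.0 or 41.5 (earlier-trial values in C.9 and C.10) and SD 10-20. A two-proportion test with 100 per arm at 0.05/15 then has about 4-6% power for a 0.25 SD difference and about 29-44% for 0.5 SD. It separates a sustained benefit from a halved one poorly, and it does not estimate a mean difference.

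**7. Precision of the proposed contrast.** The change in an arm difference between two visits with correlation r has SE √(4(1 − r)/100). Half-width at CS 0.7: 1.96 × √0.012 = 0.21 SD. At AR(1) 0.5, three steps apart, r = 0.125: 1.96 × √0.035 = 0.37 SD.

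**The case against.** A reader might infer that the plan treats a non-significant interaction as proof of a stable effect. The documents do not say so. C.6 states what follows a significant interaction and is silent on the other case. What can be said is that it offers no other rule for mean XQ.

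A reader might also infer that nothing is compared at single visits without the interaction. That is wrong too: the week-7 ANOVA and the two dichotomised outcomes at each follow-up are unconditional. C.6 also plans descriptive statistics with 95% CIs at each follow-up and says that the model will be used to examine effects over the follow-up visits. These provisions reduce the gap. They do not name a between-arm XQ difference with its interval at 10-15 months, or a change in that difference.

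Other points on this side have weight:

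- Durability is not among the listed primary or secondary aims. The C.10 sentence stands in a progress report, and end of radiotherapy is the primary time endpoint for sizing.
- Testing the interaction first is a recognised sequential strategy.
- The earlier trial against standard care showed no waning: differences of 54.5 − 44.2 = 10.3, 41.5 − 32.2 = 9.3 and 34.0 − 21.9 = 12.1 points at week 7, week 11 and 6 months.
- Disappearance of a 0.5 SD effect would usually be detected.
- An unconditional test of 0.25 SD at 10-15 months has only 42% power at 0.05, since Φ(0.25/0.1414 − 1.96) = 0.42. The gain therefore comes from estimates and intervals more than from extra tests.

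**Conclusion.** The point holds in a limited form. Mixed-model tests of mean XQ at individual time points depend on an interaction test with no stated power, and the plan specifies no other contrast for mean XQ at 10-15 months or for its change since radiotherapy ended.

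With 100 per arm, sham equal to standard care, four time points and a linear decline, that test misses a halving of 0.5 SD in about 49-83% of trials at correlation 0.5-0.7. Correlation, decline shape and sham position are assumptions. Other choices give about 33-88% over correlation 0.3-0.7, and 28% for the same linear profile at CS 0.8. Complete loss of 0.5 SD is missed in about 0.5-38% at correlation 0.5-0.7, so the weakness concerns partial waning more than disappearance.

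This is an inexpensive improvement that should be made. It does not undermine the end-of-radiotherapy comparison.

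**What to change.** Amend C.6, a. Data analysis, so that the following are reported whatever the interaction p-value, from the mixed model with time as a category:

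1. The true-minus-sham and true-minus-standard-care XQ differences with 95% CIs at every assessment, including 10-15 months.
2. The change in each difference from end of radiotherapy to 10-15 months, with its CI.

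Keep the stated Bonferroni correction for any time-point tests. Base any statement about stability on the interval in item 2, not on the interaction p-value.

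The cost is plan wording and a few contrasts from a model that will be fitted anyway; no further patients, visits or data are needed. The downside is that some intervals will be wide: about ±0.21 to ±0.37 SD for the change, before covariate or multiplicity adjustment. An interval of that width may not settle the durability question, but it shows how much waning the data leave open.

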### **a. Data analysis**

Our primary objective is to determine if true acupuncture is more effective than sham acupuncture or standard care for preventing radiation-induced xerostomia among cancer patients at M. D. Anderson and Fudan Cancer Hospital. The primary outcome will be self-reported xerostomia symptoms using the Xerostomia Questionnaire (XQ). We will have information available at baseline and at 5 additional points in time (middle of radiotherapy, end of radiotherapy, and 2-4, 5-9, and 10-15 months after the end of radiotherapy).

Our initial analysis will be a repeated-measures analysis of XQ scores over time by acupuncture group, testing for group effects, time effects, and group by time interaction. This will be done using generalized linear mixed model regression (GLMM) (see below for further details). The primary significance level which will be used is

0.05. For sample size justifications, our primary time endpoint is the end of radiotherapy, or 7 weeks. All three arms will be compared at this time point using an analysis of variance, and if the test is significant ( $p < 0.05$ ), we will use a Duncan's Multiple Range Test which controls the type I comparison-wise error rate to determine which groups are different from each other.

At each point in time, we will also be able to determine if xerostomia has occurred (grade 1 or higher on the v3.0 CTCAE) and will classify each patient as either experiencing xerostomia (one or more episodes of xerostomia) or not. A secondary goal is to determine if the proportion of persons who experience xerostomia in the true acupuncture group is less than that in the sham acupuncture group or the standard care group. We will use the

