binomial test to test for these differences at each follow-up. We will also use the clinical response criteria of determining whether or not xerostomia has occurred or not as used by Eisbruch (22) and Pacholke (74). A significant response will be indicated if the summation XQ score  $\leq$  is 30. Eisbruch and colleagues revealed with bilateral radiation therapy treatment, the peak effect of XQ xerostomia scoring at 3 months post treatment is 45 +/- 10 (22). Using the criteria of  $\leq$  30 on the XQ score, we will use the binomial test to test for these differing proportions between groups at each follow-up. However, if 15 tests are made, in order for the results to be considered as significance as those with a 0.05 significance level, the significance level would need to be 0.003 or less (0.05/15) using a conservative Bonferroni method. We will also include a GLMM analysis to evaluate treatment and time effects upon incidence (general patterns in incidence). This analysis will test the overall treatment effect, the overall time effect and a treatment by time effect.

Other outcomes include the MDASI-HN, FACT-G, USFR, SSFR, and saliva constituents including pH, buffering capacity, and viscosity as well as levels of total protein, CGRP, and VIP. These variables are repeated measurements on multiple outcomes, possibly including hierarchical structure over subscales and related outcome measures. Desired inference includes hypotheses about treatment effects at different times and on different outcomes. Also, inference about treatment effects has to appropriately adjust for recorded baseline characteristics of the enrolled patients. With these considerations in mind, we propose the following strategy for the data analysis of these variables. As we expect scores on the criterion measures to be correlated within individuals over time, we will use GLMM. Separate sets of analyses will be conducted for each criterion variable (e.g., primary outcome: severity of self-reported xerostomia symptoms (XQ); secondary outcomes: MDASI-HN, FACT-G, saliva flow rates, and saliva constituents). For each criterion variable, we will use data across the set of post-intervention assessment points. In modeling these data, intervention condition is a between-subjects factor, time is a within-subjects factor, and baseline measures will be included as covariates.

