We will also explore the association between expectancy and outcomes using information from the Acupuncture Expectancy Scale (AES). Expectancy will be assessed using the AES at baseline in the acupuncture and sham acupuncture groups and will be correlated with severity of xerostomia using the XQ (and other continuous variables) during and after radiotherapy. More complex analyses will also evaluate whether expectancy moderates outcomes. Following the procedures of Baron and Kenny (84), the evaluation of moderation involves examining the interaction between intervention condition and baseline expectancy. In a series of mixed model analyses, tests of the interaction of intervention condition with expectancy will be evaluated to determine whether baseline expectancy changes the impact of acupuncture condition on the outcome measures [i.e., determine whether acupuncture (active or inactive) is more effective based on baseline expectancy]. Changes in USFR, SSFR, and saliva constituents will also be examined as possible mediators of the effects of acupuncture on xerostomia symptoms following the procedures of Baron and Kenny (84) using generalized linear mixed model regression. The mediation effect estimate will be computed according to MacKinnon (85), who describes mediation as the difference of the intervention effect on outcome with and without the presence of the mediators, or alternatively, the product of the effect of the intervention on the mediators and the effect of the mediators on the outcome controlling for the intervention condition.

We will evaluate the data on a yearly basis by performing a yearly interim analysis. Our primary outcome is self-reported xerostomia symptoms using the Xerostomia Questionnaire (XQ). At each interim analysis, we will examine the difference in change scores (between baseline and the end of radiotherapy or 7 weeks) of the XQ between arms. If the true acupuncture arm is less effective than other arms and this comparison is statistically significant at  $< 0.001$ , we will terminate the study early (Peto method). These interim analyses will not affect the significance level of the final analysis. In order to address safety concerns, at each interim analysis we will also evaluate the incidence of grade 3 or higher adverse events in each arm separately. If patients in any arm experience more than 20% patients

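### The yearly interim harm test compares XQ change scores with no covariates named; adjusting it for baseline XQ, site and the minimisation factors would cost nothing and is never less precise in large samples

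*Supplement*

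**What the plan says.** The final protocol's C.6 a (Data analysis) sets out three analyses of XQ that bear on this point.

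- **Interim.** "We will evaluate the data on a yearly basis by performing a yearly interim analysis". The statistic is given as: "we will examine the difference in change scores (between baseline and the end of radiotherapy or 7 weeks) of the XQ between arms". The stopping condition is one of harm: "If the true acupuncture arm is less effective than other arms and this comparison is statistically significant at" 0.001, the study ends, by reference to the Peto method. The paragraph names no test, no model and no covariates, and does not say whether 0.001 is one- or two-sided.
- **Mixed model.** For each outcome, XQ included, "baseline measures will be included as covariates". The model is then extended: "we will add important covariates, including adaptive randomization variables". C.6 c calls the covariate-adjusted mixed model the primary analysis.
- **End-of-radiotherapy comparison.** "All three arms will be compared at this time point using an analysis of variance". Here too no covariates are named.

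C.3 lists the minimisation factors: stage, age, sex, planned mean parotid dose (left and right), induction therapy and concurrent chemotherapy. Randomisation is run separately at each site. C.2 excludes patients with a history of xerostomia.

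**The concern.** Subtracting baseline fixes the slope of end-of-radiotherapy XQ on baseline XQ at 1. Adjusting for baseline estimates that slope from the data. If the true slope is not 1, subtraction leaves avoidable noise in the comparison. Patients enter without a history of xerostomia, and the score is then driven up by radiation, so there is no particular reason to expect a slope of 1.

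The minimisation factors matter separately. Section A (Significance) itself ties xerostomia to how much salivary tissue is irradiated, so parotid dose should be prognostic. Leaving it out costs precision whatever the spread of baseline XQ.

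This rule protects patients if true acupuncture makes dry mouth worse. It works at a strict threshold and on the smallest samples of the trial. Extra noise makes it more likely that a harmful effect passes a yearly look undetected.

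**Working it through.** **The plan's own figure.** C.6 c says: "Assuming a two- sided significance level of 0.05, we will have at least 80% power to detect differences between any pair of group means". The difference is set at 0.4 SD, with 100 per group. The normal approximation gives Φ(0.4/√(2/100) − 1.96) = 80.7%, so the figure reproduces. No power is stated for the interim boundary, so there is no interim figure to reproduce.

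**Variances.** Set the end-of-radiotherapy SD to 1, the baseline SD to k and their correlation to ρ.

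- Change score: V_c = 1 + k² − 2ρk
- Baseline-adjusted: V_a = 1 − ρ²
- Excess: V_c − V_a = k² − 2ρk + ρ² = (k − ρ)²

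The excess is never negative and is zero only when k = ρ, that is, when the slope ρ/k equals 1.

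**Sample at each look (assumed; the plan gives none).** C.2 expects 50 evaluable patients per institution per year. That is 2 × 50 / 3 ≈ 33 per arm after one year and 2 × 100 / 3 ≈ 67 after two. As a cross-check, recruiting 70 per institution per year with 31% drop-out gives 2 × 70 × 0.69 / 3 ≈ 32 per arm after one year.

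**Power for one pairwise comparison.** Power = Φ(d/√(2V/n) − 3.29), where 3.29 is the two-sided 0.001 critical value (two-sided assumed) and d is the worsening in end-of-radiotherapy SDs. The values of d, k and ρ are assumptions. For example, at k = 1, ρ = 0.5, n = 33, d = 0.8:

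- Change score: Φ(0.8/√(2 × 1.00/33) − 3.29) = Φ(3.25 − 3.29) = 48%
- Adjusted: Φ(0.8/√(2 × 0.75/33) − 3.29) = Φ(3.75 − 3.29) = 68%

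| k | ρ | V_c | V_a | n = 33, d = 0.8: change → adjusted | n = 67, d = 0.5: change → adjusted |
|---|---|---|---|---|---|
| 0.2 | 0.2 | 0.96 | 0.96 | 51.0% → 51.0% | 36.8% → 36.8% |
| 0.3 | 0.1 | 1.03 | 0.99 | 46.5% → 49.0% | 33.0% → 35.1% |
| 0.3 | 0 | 1.09 | 1.00 | 42.9% → 48.4% | 30.2% → 34.6% |
| 0.1 | 0.5 | 0.91 | 0.75 | 54.6% → 67.8% | 39.9% → 52.0% |
| 0.5 | 0.3 | 0.95 | 0.91 | 51.7% → 54.6% | 37.4% → 39.9% |
| 0.5 | 0.5 | 0.75 | 0.75 | 67.8% → 67.8% | 52.0% → 52.0% |
| 1 | 0.5 | 1.00 | 0.75 | 48.4% → 67.8% | 34.6% → 52.0% |
| 1 | 0.3 | 1.40 | 0.91 | 29.3% → 54.6% | 19.9% → 39.9% |

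With k and ρ both at most 0.3, the gain is about 0 to 6 points. At k = 1, ρ = 0.5 it is 19 and 17 points.

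**Minimisation factors.** No R² is given, so this is illustration only. Take k = ρ = 0.3, where baseline adjustment alone gains nothing (V = 0.91). If the factors explained 10% to 20% of the remaining variance, V would be 0.82 to 0.73. Power would then rise from 54.6% to 62–70% at the first look and from 39.9% to 46–54% at the second.

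**Type I error.** In 20,000 simulated null trials per setting with 100 per arm, the change-score test rejected 0.047 to 0.051 of the time at 0.05, and 0.0009 to 0.0014 at 0.001. That is about nominal.

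**The case against.** The strongest reply is that the plan does not exclude adjustment. The interim paragraph names an outcome and stops there. Analysing change with baseline as a covariate gives exactly the same treatment effect as analysing the final score with baseline as a covariate, so the wording is compatible with an adjusted test. This stands to the extent that the absence of covariates is read from silence. Even so, a plain comparison of change scores is the natural reading, and a stopping rule should not leave its test open.

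Second, the loss may be very small. The exclusion of prior xerostomia suggests low, tightly grouped baseline scores, and the large gains in the table at k = 1 require baseline XQ to vary as much as end-of-radiotherapy XQ. This stands. A reader might go further and infer that a narrow baseline removes the problem, but it does not: at k = 0.1, ρ = 0.5 the loss is 12 to 13 points. What matters is whether k equals ρ. The loss from leaving out parotid dose does not depend on baseline spread at all.

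Third, a reader might infer that the interim test is out of step with every final analysis. It is not: the end-of-radiotherapy analysis of variance also names no covariates. The contrast is with the mixed model only.

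Finally, the boundary is deliberately conservative, the plan claims no power for it, and the test is valid. All of that is correct, which is why this is a point about efficiency.

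**Conclusion.** The point holds as a minor one. As written, the interim harm rule uses a change score with no covariates named, while the plan's primary mixed model adjusts for baseline XQ and the minimisation variables. In large samples the change score is never more precise than baseline adjustment, and the two are equal only when k = ρ.

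The size of the loss cannot be settled from the documents, because k, ρ, the variance explained by the minimisation factors and the sample at each look are all missing. On the assumptions above, baseline adjustment is worth about 0 to 6 power points if k and ρ are both at most 0.3, which the entry criteria make plausible. It is worth 17 to 19 points at k = 1, ρ = 0.5. Any gain from parotid dose and the other factors would be additional.

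The documents do not support reading this as bias, as inflated type I error, or as an established material loss of protection for patients.

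**What to change.** In C.6 a, state that each interim look compares end-of-radiotherapy XQ (or, equivalently, its change from baseline) between arms in a linear model, with baseline XQ, site and the minimisation factors as covariates. State also whether 0.001 is one- or two-sided. Leave the 0.001 boundary and its direction as they are.

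Enter planned parotid dose as a continuous value for each side. The nine bands per side in C.3 would use 16 degrees of freedom, against 2 for continuous values, which matters at about 33 patients per arm.

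For consistency, use the same adjusted model for the end-of-radiotherapy comparison now written as an analysis of variance.

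The cost is a sentence or two in the plan. Baseline XQ is collected before randomisation, and site and the minimisation factors are known at randomisation, so no patients, visits or measurements are added.
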